### Participants

Middle–aged and older adults deemed eligible to participate in the intervention groups of AKETS were enrolled from the AKS cohort if they satisfied the following inclusion criteria: (1) aged 40–90 years; (2) estimated glomerular filtration rate (eGFR) calculated based on serum cystatin C levels > 30 mL/min/1.73 m^2^; (3) no restrictions on exercise imposed by a medical doctor; (4) no current severe illnesses or significant past medical history; (5) agreement to the terms and conditions of the medical fitness center; and (6) absence of issues that would affect participation in the study. Participants with contraindications (e.g., neurological and walking problems) to exercise training are excluded. Individuals interested in participating are provided with written and oral information from the researchers regarding the study aims, procedures, confidentiality of personal information, possible benefits and risks, and coping strategies. Only participants who provide written informed consent were included in the current trial. A total of 203 middle–aged and older adults who met the eligibility criteria received invitation letters and emails. Of them, 141 participated in the baseline assessment, whereas the remaining 62 declined to participate for personal reasons such as work commitments, lack of time, and living too far away to regularly attend the fitness center.

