Several cross–sectional studies have reported that individuals with higher levels of physical activity and performance tend to have better kidney function [14–18]. Furthermore, longitudinal studies have demonstrated an independent association of physical activity and fitness with preventing CKD development and rapid kidney function decline [19–23]. Recent evidence from animal model studies also indicates the potential renoprotective effects of long–term exercise training in various CKD models [24–28]. These epidemiological and basic findings suggest that exercise training aimed at improving physical activity and fitness could be an effective strategy for preventing CKD development [29, 30]. However, it remains possible that declines in kidney function may lead to reduced muscle mass and impaired physical performance, subsequently resulting in lower physical activity levels (i.e., reverse causation). Indeed, evidence in humans from the limited number of randomized controlled trials (RCTs) investigating whether exercise training benefits kidney health has been inconsistent [31–34]. Therefore, the renoprotective effects of exercise training remain uncertain and controversial, highlighting the need for rigorously designed interventional studies to clarify causality.

The inconsistent findings from exercise–nephrology RCTs may stem from the possibility that kidney aging is irreversible and progresses slowly with significant individual variations. Thus, when investigating the effects of exercise training on kidney health, within–group (intra–individual) comparisons may be more critical than between–group (inter–individual) comparisons. To achieve both comparisons, the trial within cohorts (TwiCs) study design, in which the intervention study is performed within a prospective observational cohort with regular measurements [35, 36], is considered more appropriate than conventional standard RCTs. The TwiCs study design allows for an evaluation of not only within–group changes and between–group differences but also the long–term effects of exercise training intervention, because regular measurements in the prospective cohort will be continued after the completion of the intervention period [37].

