### Randomization and blinding

Participants are to be classified into one of the following three groups: (1) exercise intervention group, (2) stretching intervention (active control) group, and (3) usual lifestyle (time control) group (Fig. 2). Participants voluntarily choose to enroll in either the usual lifestyle group or one of two intervention groups (exercise or stretching). Assignment to the usual lifestyle or intervention group is determined based on participant preference and collected via a questionnaire administered after obtaining written informed consent. Only those who opt for the intervention arm are subsequently randomized into one of the two groups (i.e., exercise or stretching group). Randomization within the intervention arm is stratified by age, sex, and GFR stage and performed using a computer–generated randomization sequence following the completion of baseline assessments. The allocation ratio between the two intervention groups is 1:1. The random allocation sequence was generated by a study statistician (MG). Allocation of participants was conducted by an independent study investigator (YN) who had no direct contact with participants. Personnel involved in participant enrollment (KK) did not have access to the random allocation sequence at any stage, ensuring adequate allocation concealment. The investigators responsible for evaluating the primary outcome are independent of the study team and remain blinded to group allocation throughout the study period. However, due to the inherent characteristics of the interventions (structured exercise training versus stretching) and the need to describe the intervention procedures in the informed consent documents and study protocol, blinding participants to group allocation was not feasible. To mitigate the risk of performance bias, we standardized the frequency, duration, and monitoring procedures of both intervention programs.

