### Primary and secondary outcome measures

The primary outcome of this study is the annualized rate of change in eGFR (i.e., eGFR slope), expressed as mL/min/1.73 m² per year. Based on findings from a recent meta–analysis of RCTs, the eGFR slope is recognized as a reliable surrogate endpoint for tracking CKD development [45, 46]. Given that serum cystatin C levels are less influenced by physical activity and muscle mass than serum creatinine levels [47], serum cystatin C levels are used to calculate the eGFR and evaluate changes in kidney function. The eGFR slope is determined using a linear mixed–effects model with random intercepts [48].

The secondary outcomes include alterations in renal hemodynamics and oxygenation assessed using Doppler ultrasound imaging and MRI, glomerular and tubular damage biomarkers, cardiovascular function indices, such as arterial stiffness and endothelial function, blood– and urine–based markers of mineral and bone metabolism, body composition and bone density, muscle strength, cardiorespiratory fitness, physical performance, habitual dietary intake, sedentary behavior, physical activity, sleep quality, and mental health. The detailed measurement methods for the secondary outcomes are provided in the Supplementary Material.

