As a sensitivity analysis, multiple imputations will be applied to the missing outcome data to assess the robustness of the findings from the above analyses. In addition, pre–specified subgroup analyses based on baseline characteristics will be performed to further explore potential effect modification. Specifically, subgroup analyses will be conducted according to baseline kidney function (eGFR < 60 mL/min/1.73 m²), glycemic control status (hemoglobin A1c ≥ 6.5%), hypertension status (systolic blood pressure ≥ 140 mmHg and/or diastolic blood pressure ≥ 90 mmHg), and obesity/overweight (body mass index ≥ 25 kg/m²).

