## Discussion

With the rapid aging of the population, the recent predominant demographics of patients has also shifted towards middle–aged and older adults [3]. In this context, the current cases of CKD are mainly associated with the long–term affliction of lifestyle–related diseases, such as diabetes, hypertension, and arteriosclerosis/atherosclerosis. In addition to these pathophysiological trends, considering the progressive nature of CKD without apparent symptoms [5], there is a growing focus on implementing early preventive strategies to minimize the kidney function decline. Numerous epidemiological pieces of evidence demonstrating the independent association of physical activity, performance, and fitness with development in CKD suggest that addressing physical inactivity through regular exercise practices may play a crucial role in preventive strategies against CKD in middle–aged and older adults [29, 30]. However, there is a significant lack of evidence from interventional studies examining whether regularly performed exercise benefits aging kidney health. This TwiCs study will provide intra– and inter–individual comparisons between sedentary and active lifestyles, incorporating regular physical activity and exercise, offering insights into their impact on kidney health in middle–aged and older adults. We will also investigate the residual effects of exercise training intervention throughout the 1–year observation period, as such findings may help understand the potential of sustained preventive strategies for CKD.

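### The Discussion's sedentary-versus-active claim is not backed by eligibility or the eGFR models, and baseline activity is left as an unadjusted possible confounder against the self-chosen usual-lifestyle group

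*Protocol article*

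**What the plan says.** - **Claim (Discussion, first paragraph).** The study is to give, within and between individuals, "comparisons between sedentary and active lifestyles, incorporating regular physical activity and exercise".
- **Eligibility (Participants).** There are six inclusion criteria, plus an exclusion for contraindications to training. The two that come nearest to activity read "3) no restrictions on exercise imposed by a medical doctor; (4) no current severe illnesses or significant past medical history". None limits habitual exercise.
- **Comparators.** Usual-lifestyle participants are asked to carry on with their existing habits. The stretching programme's description sets no limit on other activity.
- **Allocation (Randomization and blinding).** Participants choose between usual lifestyle and the intervention arm. Only the latter are randomised: "Randomization within the intervention arm is stratified by age, sex, and GFR stage", and "The allocation ratio between the two intervention groups is 1:1".
- **eGFR models (Statistical analysis).** The primary mixed model has group (all three), time, group by time and baseline eGFR, with participant as a random effect. A further ANCOVA adjusts for the pre-intervention eGFR slope.
- **Subgroups (Statistical analysis).** "Specifically, subgroup analyses will be conducted according to baseline kidney function", and then glycaemic control, hypertension and overweight. Activity is not listed.
- **Activity data.** Accelerometry follows the laboratory assessments (Measurements). The secondary outcomes include "habitual dietary intake, sedentary behavior, physical activity, sleep quality, and mental health".
- **Rationale (Introduction).** Longitudinal studies are cited as showing an "independent association of physical activity and fitness with preventing CKD development and rapid kidney function decline".
- **Comparability.** The limitations paragraph of the Discussion answers the concern about self-selection by pointing to Table 1. That table lists demographic, body-size, blood and haemodynamic variables and no measure of activity.

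**The concern.** A sedentary-versus-active comparison needs participants who were inactive before training and comparators who stay inactive. The article secures neither. Someone who already exercises regularly can enter any of the three groups. For that person, the training year against the earlier years is not a move from inactive to active.

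Two things are at stake. The first is description: a positive result could be reported as a sedentary-versus-active effect when the contrast was really a programme added to whatever people already did.

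The second is confounding. The primary model includes a group formed by preference, and existing exercise habits are a plausible reason for choosing or declining a fitness-centre programme. By the article's own rationale those habits also predict kidney decline. Such a variable should be examined and adjusted for in a non-randomised comparison. Here it is measured, but it is not used for that purpose.

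**Working it through.** **1. Where baseline activity could enter, and whether it does**

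| Place | Variables named | Baseline activity? |
|---|---|---|
| Eligibility | age, eGFR, medical restriction, illness, centre terms, other issues | no |
| Stratification | age, sex, GFR stage | no |
| Primary eGFR model | group, time, group by time, baseline eGFR | no |
| ANCOVA of slopes | group, pre-intervention slope | no |
| Listed subgroups | eGFR, HbA1c, blood pressure, BMI | no |
| Table 1 | demographic, body-size, blood, haemodynamic | no |
| GEE for secondary outcomes | group, time point including baseline, interaction | yes, as an outcome |
| Correlations of individual changes | changes in each outcome | only through change |

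Activity is therefore analysed as an outcome and as a change. It is not a covariate or effect modifier for eGFR slope.

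**2. Which comparisons are affected**

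Suppose a participant's slope shifts by γ per unit of baseline activity, and mean baseline activity differs by Δ between two groups. With a linear relation and no adjustment, the slope difference carries a bias of γ × Δ.

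- Exercise versus stretching: randomisation makes the expected Δ zero, so there is no bias.
- Either arm versus usual lifestyle: Δ depends on who chose what. The article gives neither γ nor Δ, so the bias cannot be sized. Table 1 cannot show that Δ is small.

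Because the outcome is a slope, a main effect of activity would shift only the eGFR level. Adjusting the slope comparison requires activity by time.

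**3. The plan's sample size, and an illustration of a smaller contrast**

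Inputs from Sample size calculation: difference 5, SD 8, two-sided 0.05, power 0.80. A two-sample t-test gives 41.17, so 42 per arm and N = 2 × 42 = 84. This matches the stated figure exactly. The normal approximation gives 41 per arm, N = 82.

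Illustration: assume a share f of participants gains nothing and the rest gain the planned 5. The difference is then 5 × (1 − f), with SD held at 8. With the Table 1 arms the standard error is 8 × √(1/43 + 1/45) = 1.706, on 43 + 45 − 2 = 86 degrees of freedom. **The documents do not give f.**

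| f | Difference | Power, 43 vs 45 | N for 80% power |
|---|---|---|---|
| 0% | 5.0 | 82.6% | 84 |
| 10% | 4.5 | 74.2% | 102 |
| 20% | 4.0 | 64.0% | 128 |
| 30% | 3.5 | 52.7% | 166 |
| 40% | 3.0 | 41.3% | 226 |
| 50% | 2.5 | 30.5% | 324 |

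The table shows sensitivity to an assumption. It is not an estimate of what will happen.

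**The case against.** The strongest reply is that one loose Discussion sentence is not the trial's question. The stated aim is whether a training programme slows kidney decline, and the first hypothesis compares decline during training with earlier decline in the same people. Neither needs inactive participants, and broad entry is a legitimate choice in a community trial. That stands. The point concerns a claim and a covariate, not eligibility.

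A reader might infer that already-active people do dilute the randomised contrast. The documents do not support that. They show only that such people are not excluded, and they report no activity data. The programme is individualised and progressive, with machine loads set from each person's own maximum and reassessed at 6 months, so an active person may still gain. Assuming exactly no gain is severe.

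A reader might also infer that the plan could not tell an ineffective programme from an unchanged exposure. That is wrong too. The GEE will show whether activity changed differently by group, individual changes will be correlated in line with the second hypothesis, and adherence is recorded. These analyses do not, however, adjust the usual-lifestyle comparison or test whether the randomised effect depends on starting activity.

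The ANCOVA on pre-intervention slope may absorb some of the influence of long-standing habits. It is an additional comparison, though, and the primary mixed model has no such term.

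Finally, extra covariates are often left to an analysis plan that is not shown here. But the article itself names the model terms and the subgroups, and rests comparability on Table 1, so the choice is open to comment.

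**Conclusion.** The point holds in a limited form. The sedentary-versus-active wording is supported neither by eligibility nor by any use of baseline activity in the eGFR analyses. The clearer risk is confounding in comparisons with the usual-lifestyle group. Its size is unknown because the article reports neither the difference in activity between groups nor the strength of its relation to slope.

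Exercise versus stretching remains unbiased. Loss of contrast there is possible, but its size cannot be established; the fall in power from 83% to 64% at f = 20% rests wholly on an assumed share with no gain. The sample size arithmetic is correct. It would overstate the matter to say that no activity comparison is planned at all. This is a cheap improvement.

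**What to change.** 1. **Covariate.** Add baseline accelerometer activity, kept continuous (for example, moderate-to-vigorous minutes per day), and its interaction with time to the eGFR slope model, at least for comparisons involving the usual-lifestyle group. This reduces confounding by measured activity. It does not remove other differences between people who chose differently, and it does not restore a reduced contrast.
2. **Effect modifier.** Add baseline activity to the prespecified list as a continuous group by time by activity term in exercise versus stretching. Label it exploratory and state that its power is low with 88 randomised.
3. **Wording.** In the Discussion, describe the contrast as *usual activity versus usual activity plus the exercise programme*, unless the baseline data show that participants were inactive. Reporting baseline activity by group beside Table 1 would settle this and would support or weaken the comparability statement.

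The cost is a few lines of analysis text and one reworded sentence, using data already collected. The downside is one more low-powered exploratory analysis in a trial that does not control multiplicity for its secondary analyses. Specifying the terms before outcomes are analysed avoids their looking post hoc.

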### Randomization and blinding

Participants are to be classified into one of the following three groups: (1) exercise intervention group, (2) stretching intervention (active control) group, and (3) usual lifestyle (time control) group (Fig. 2). Participants voluntarily choose to enroll in either the usual lifestyle group or one of two intervention groups (exercise or stretching). Assignment to the usual lifestyle or intervention group is determined based on participant preference and collected via a questionnaire administered after obtaining written informed consent. Only those who opt for the intervention arm are subsequently randomized into one of the two groups (i.e., exercise or stretching group). Randomization within the intervention arm is stratified by age, sex, and GFR stage and performed using a computer–generated randomization sequence following the completion of baseline assessments. The allocation ratio between the two intervention groups is 1:1. The random allocation sequence was generated by a study statistician (MG). Allocation of participants was conducted by an independent study investigator (YN) who had no direct contact with participants. Personnel involved in participant enrollment (KK) did not have access to the random allocation sequence at any stage, ensuring adequate allocation concealment. The investigators responsible for evaluating the primary outcome are independent of the study team and remain blinded to group allocation throughout the study period. However, due to the inherent characteristics of the interventions (structured exercise training versus stretching) and the need to describe the intervention procedures in the informed consent documents and study protocol, blinding participants to group allocation was not feasible. To mitigate the risk of performance bias, we standardized the frequency, duration, and monitoring procedures of both intervention programs.

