### Intervention

#### Exercise intervention group

Participants assigned to the exercise training group participate in an individualized, progressive, multicomponent training program based on the official exercise guidelines of the Japanese Ministry of Health, Labour, and Welfare (https://www.mhlw.go.jp/content/000656460.pdf). The program includes aerobic, resistance, and balance training and is conducted either under supervision at the Medical Fitness Center Phoenix (Tsukuba, Ibaraki, Japan) or unsupervised at home. The participants are instructed to exercise at least three times per week for approximately 60 min per session, with at least one session per week performed under supervision. In addition to each exercise session, warm–up and cool–down activities for approximately 15 min are included. During supervised aerobic sessions, the participants perform 20 min activities using a treadmill or cycle ergometer at an intensity of 50–70% of their age–predicted maximum heart rate calculated using the Tanaka formula (i.e., 208 − 0.7 × age) [44], corresponding to a perceived exertion of “somewhat hard.” Supervised resistance training consists of five machine–based exercises—namely, chest press, seated rowing, leg press, leg curl, and leg extension. Each exercise is performed in 2–3 sets of 10–12 repetitions at 30–70% of the one–repetition maximum (1–RM). The exercise dose (i.e., load, repetitions, and sets) is progressively adjusted based on the participant’s adaptation. The exercise load for months 0–6 is determined using baseline 1–RM, whereas the exercise load for months 7–12 is based on reassessment at 6 months. In unsupervised sessions, participants are encouraged to engage in aerobic activities such as walking, bodyweight resistance exercises (e.g., squats and push–ups), and balance exercises (e.g., front lunges and heel raises). The heart rate is monitored and recorded in real time during all sessions using a wrist–worn device (Xiaomi Smart Band 9, Xiaomi Japan, Tokyo, Japan). To monitor adherence, the participants are required to complete a daily exercise training log documenting their pre–exercise blood pressure, subjective condition, exercise type, duration, and heart rate. Exercise training logs are collected monthly at the Medical Fitness Center Phoenix (Tsukuba, Ibaraki, Japan) and reviewed to assess compliance with the prescribed program. When necessary, follow–up support is provided via telephone or in–person meetings to encourage sustained engagement.

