
#### Stretching intervention group (Active control group)

To maintain participant motivation and ensure ethical requirements, an active control group is established and provided with a structured stretching intervention program. This program consists of 20 static stretching exercises targeting major muscle groups in the upper body, trunk, and lower body and is designed to minimize cardiovascular load by minimizing heart rate elevation. Following randomization, the participants attend an orientation session in which a certified instructor explains each stretch movement and the procedures for the logging activity. The stretching program is designed to be performed for 10–20 min per session. During the first six months, both the number of stretching exercises and the total session duration are progressively increased. The participants are instructed to perform stretching exercises at home at least three times per week. To monitor adherence, completed stretching logs are collected monthly and reviewed by study personnel.

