### Assessment of adverse events and adherence

Adverse events will be monitored continuously throughout the study period via monthly participant check–ins, standardized questionnaires, and review of training logs. All reported adverse events will be categorized systematically, with serious adverse events being promptly reviewed by independent clinical advisors. Serious adverse events will be classified if they result in death, are immediately life–threatening, require inpatient hospitalization, or lead to persistent or significant disability/incapacity. Affected participants are free to discontinue the trial or continue with the intervention. Adherence to the intervention, including the frequency and intensity of exercise and stretching (both supervised and home–based), throughout the 12–month intervention period will be assessed using a self–recorded exercise and stretching diary. If a participant drops out of the intervention program, the reasons will be recorded.

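### The claim that frequency, duration and monitoring were standardised across the exercise and stretching programmes holds only in part: session time differs about three-fold or more, and some monitoring is described for exercise alone

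*Protocol article*

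**What the plan says.** The Randomization and blinding section states that "blinding participants to group allocation was not feasible" and then, as the step taken against performance bias, that "we standardized the frequency, duration, and monitoring procedures of both intervention programs". It also says that those evaluating the primary outcome "remain blinded to group allocation throughout the study period".

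The Exercise intervention group section asks participants to "exercise at least three times per week for approximately 60 min per session", "with at least one session per week performed under supervision". On preparation and recovery it adds: "In addition to each exercise session, warm–up and cool–down activities for approximately 15 min are included". It also describes wrist-device heart-rate recording at every session, a daily log that includes blood pressure and heart rate, monthly log collection and review, and telephone or face-to-face support when needed.

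The Stretching intervention group section sets sessions of 10–20 min, with the number of stretches and the session length rising over the first six months. Setting and frequency are given thus: "The participants are instructed to perform stretching exercises at home at least three times per week". An instructor-led orientation comes first, and logs are collected and reviewed monthly.

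The section on adverse events and adherence covers both programmes over the same 12 months by self-kept diary, "including the frequency and intensity of exercise and stretching (both supervised and home–based". It also describes monthly check-ins for adverse events, without separating the arms.

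**The concern.** Exercise versus stretching is the only randomised comparison in the trial; the usual lifestyle group is self-selected. Because participants are unblinded, the credibility of that comparison depends partly on how alike the two programmes are in everything other than exercise. The standardisation sentence is the only measure the article offers against performance bias. Blinded evaluation of the primary outcome addresses detection bias, and the stretching arm itself is justified by motivation and ethics.

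A reader who relies on that sentence would take session time and monitoring to be equal between arms, and would attribute a difference in eGFR slope, or in diet, sleep, activity or mental health, to exercise itself. If the arms also differ in staff contact, self-measurement and encouragement, a difference could arise partly through changes in participants' behaviour outside the exercise sessions. The Discussion lists five limitations, and this is not among them.

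**Working it through.** The article gives no figure of its own for how alike the programmes are, so there is nothing to reproduce. The check compares each of the three items said to be standardised with the two intervention sections.

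**1. Frequency.** Exercise: at least 3 sessions a week. Stretching: at least 3 a week. Ratio 3/3 = 1. This item matches.

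**2. Duration, read as session length.** Inputs: exercise about 60 min; warm-up and cool-down about 15 min, with wording that leaves open whether they fall inside or outside the 60 min; stretching 10–20 min.

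| Exercise session | Stretching session | Ratio | Minimum weekly minutes (3 × session) |
|---|---|---|---|
| 60 min | 20 min | 60/20 = 3.0 | 180 vs 60 |
| 60 min | 10 min | 60/10 = 6.0 | 180 vs 30 |
| 60 + 15 = 75 min | 20 min | 75/20 = 3.75 | 225 vs 60 |
| 60 + 15 = 75 min | 10 min | 75/10 = 7.5 | 225 vs 30 |

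Stretching sessions lengthen over the first six months, so the 10-min rows presumably describe the early phase. If later sessions run at 20 min, the 20-min rows (3.0 to 3.75) describe that period better. This item does not match on any row.

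**3. Duration, read as programme length.** The adherence section gives a common 12-month intervention period. On this reading the item matches.

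**4. Monitoring procedures.**
- Described for both arms: logs or diaries kept by participants, monthly log collection and review, and monthly adverse-event check-ins not split by arm.
- Described for exercise only: real-time heart-rate recording at all sessions, blood pressure and heart rate in the log, and telephone or face-to-face support when needed.

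These differences are of kind, so no ratio can be formed. The item matches in part.

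**5. Supervision, which the sentence does not list.** Exercise: at least one supervised session a week. Stretching: home sessions after orientation. The adherence wording refers to supervised and home-based sessions without saying which arm has which, so whether any stretching is supervised is unclear.

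**The case against.** The strongest reply is that much of the sentence is true. Frequency matches, log review matches and the 12-month period is shared, so performance bias is not left wholly uncontrolled. That stands. A reader might infer from the session times that the claimed control does not exist at all; the documents do not support this.

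A second reply concerns supervision. A reader might treat weekly supervision as another contradiction, or count about 52 supervised contacts a year against one orientation. Neither holds. The sentence does not claim equal supervision, the adherence section leaves supervised stretching unclear, and the count ignores the monthly check-ins. Unequal supervision is a separate concern about contact.

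Third, part of the monitoring gap rests on silence. The stretching section does not mention a wrist device, blood-pressure logging or support calls, but it does not exclude them, and a journal article condenses. This stands as a caution: these elements can only be called described for exercise alone.

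Fourth, the sentence may bear a milder meaning. Duration could be programme length, and standardised could mean fixed by protocol within each programme. Beside frequency, session length is the more natural reading, and neither alternative serves the stated purpose: equal programme length does little about unequal time and contact, and only likeness between arms mitigates performance bias.

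Fifth, exercise minutes are part of the treatment and stretching is deliberately light, so unequal time is not in itself confounding. This is right. What threatens attribution is the contact, monitoring and encouragement that come with the exercise programme. No size for that effect on a cystatin C-based slope can be derived from the documents.

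**Conclusion.** The standardisation claim is wrong as written, but only in part. Minimum frequency, monthly log collection and review, and the 12-month period are common to both arms. Session time differs by a factor of 3 to 7.5 across the stated ranges, or 3 to 3.75 at the 20-min end of stretching, and the monitoring described is only partly alike. This rests on two assumptions: that duration means session length, and that the intervention sections describe the programmes as delivered. The upper figure also assumes that the 15 min is added to the 60 min and that stretching is at its 10-min lower end.

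The consequence is for interpretation. The randomised contrast compares an exercise programme, with the supervision and contact described for it, with a brief home stretching programme; a difference between arms would not isolate exercise. Blinded evaluation of the primary outcome does not remove this, because unequal contact can act on participants' behaviour. A reader might go further and conclude that the randomised comparison is invalid or the result biased by a known amount; nothing in the documents supports that. Randomisation, sample size and the primary analysis are unaffected.

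**What to change.** - Reconcile the Randomization and blinding section with the two intervention sections and the adherence section. Say whether duration means session or programme length, whether warm-up and cool-down fall within the 60 min, and whether any stretching is supervised.
- Replace the standardisation claim with a statement of what was matched (on the present text: minimum frequency, programme length, monthly log collection and review) and what was not (session time and, if confirmed, supervised contact, heart-rate and blood-pressure recording, and follow-up support).
- State that the randomised contrast is interpreted as the whole exercise programme, including its supervision and contact, against the brief home stretching programme.
- Add unequal contact and monitoring to the limitations in the Discussion.
- Summarise session time and supervised contacts by arm as far as existing records allow. The exercise log records duration; the article does not say whether the stretching log does.

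Comparisons of diet, physical activity and sedentary behaviour between arms are already planned as secondary outcomes and need no addition. No change to either programme is proposed. The cost is text and one short descriptive summary; the price is a more modest claim about what can be attributed to exercise itself.
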